#### 5 Research Institutions and their Responsibilities

This trial is funded by the National High-Tech Research and Development Program of China (863 Program) and is supervised by the Clinical Pharmacology Trial Ethics Review Committee of Peking Union Medical College Hospital and the Ethics Review Committee of the National Center for AIDS/STD Control and Prevention (NCAIDS). The primary research institutions participating in the clinical trial and their responsibilities are listed in Table 4.

### 5.1 Responsibilities of Sponsor(s)

The National Center for AIDS/STD Control and Prevention (NCAIDS) and the Beijing Institute of Biological Products are the sponsors of the clinical trial, with responsibilities as follows:

- (1) To recognize the qualifications and conditions of the investigators at the clinical trial sites to ensure the completion of the trial;
- (2) To provide the clinical trial sites with an investigator's brochure, containing pharmaceutical, toxicological, and preclinical experimental data and information on the test vaccine;
- (3) To initiate the clinical trial in accordance with this protocol after obtaining approval from the National Medical Products Administration and consent from the ethics committee;
- (4) To collaborate with the investigators in designing the clinical trial protocol, specifying responsibilities in data processing, statistical analysis, results reporting, and publication methods, as well as the division of labor agreed upon with the investigators. To sign the mutually agreed trial protocol and contract;
- (5) To assist investigators in recruiting subjects;
- (6) To provide investigators with the test vaccine and instructions for use, ensuring the quality of the vaccine is qualified. To establish a management system and recording system for the registration, storage, and distribution of the test vaccine;
- (7) To appoint monitors acceptable to the investigators to oversee the progress of the clinical trial;
- (8) To be responsible for establishing a quality control and quality assurance system for the clinical trial. If necessary, to organize audits of the clinical trial to ensure quality;
- (9) To collaborate with investigators in promptly studying any serious adverse events that occur, taking necessary measures to ensure the safety of subjects, and reporting to the drug regulatory authorities in a timely manner, while also informing other investigators involved in clinical trials of similar vaccines about the adverse events;

- (10) To promptly notify investigators, the ethics committee, and the National Medical Products Administration of any early termination or suspension of the clinical trial, stating the reasons;
- (11) To submit a summary report of the trial to the National Medical Products Administration, or a report on the termination of the trial and the reasons thereof;
- (12) To be responsible for covering the costs of treatment or management for injuries or deaths caused by vaccination during the clinical trial, and to provide appropriate financial compensation to those who experience severe adverse reactions. To provide subjects with accidental injury insurance during the trial period;
- (13) If an investigator does not comply with the approved protocol, Good Clinical Practice (GCP), or relevant regulations during the clinical trial, the sponsor should point this out to seek correction. If the situation is serious or persists, the sponsor should terminate the investigator's participation in the clinical trial and report to the National Medical Products Administration.

## **5.2 Responsibilities of Investigator(s)**

Peking Union Medical College Hospital is the investigator for this clinical trial, with responsibilities as follows:

- (1) The research personnel participating in the clinical trial should be familiar with Good Clinical Practice (GCP) and adhere to national laws, regulations, and ethical standards. They should have extensive experience in clinical trial methodology or receive academic guidance from experienced researchers within their institution, and possess the professional knowledge and experience required by the trial protocol;
- (2) Be familiar with the materials and literature related to the clinical trial provided by the sponsor; understand and be familiar with the nature, effects, and safety of the investigational vaccine (including relevant data from preclinical studies), and also keep abreast of all new information related to the vaccine that arises during the course of the clinical trial;
- (3) Have and be able to allocate the necessary personnel and equipment for the trial; possess all facilities to handle emergencies to ensure the safety of the subjects;
- (4) Laboratory testing methods must be nationally certified, and laboratory results must be accurate and reliable;
- (5) Must thoroughly read and understand the contents of the trial protocol, co-sign the clinical trial protocol with the sponsor, and strictly adhere to the protocol's stipulations; must promptly submit the clinical trial protocol and informed consent forms to the ethics committee for approval;
- (6) Must obtain the consent of the hospital to ensure sufficient time is available to responsibly complete the clinical trial within the protocol's specified timeframe; must explain the trial's information, regulations, and responsibilities to all staff

- involved in the clinical trial, ensuring an adequate number of informed and eligible subjects are enrolled according to the trial protocol;
- (7) Take necessary measures to protect the safety of subjects and document these measures. Be responsible for making medical decisions related to the clinical trial, ensuring that subjects receive appropriate treatment for any adverse events that occur during the trial;
  - (8) In the event of a serious adverse event during the clinical trial, immediately provide appropriate treatment to the subject, report to the drug regulatory authorities, the sponsor, and the ethics committee, and sign and date the report;
  - (9) Ensure that subject data is accurately, completely, timely, and lawfully recorded in the case report forms;
  - (10) Accept monitoring and auditing by the sponsor's monitors or auditors, as well as inspections by the drug regulatory authorities, to ensure the quality of the clinical trial;
  - (11) Upon completion of the clinical trial, the investigator must write a summary report, sign and date it, and then send it to the sponsor;
  - (12) Must notify subjects, the sponsor, the ethics committee, and the National Medical Products Administration of any early termination or suspension of the clinical trial, stating the reasons.

### **5.3 Responsibilities of Data Management Center**

The Health Statistics Office of the Chinese Center for Disease Control and Prevention (CDC) will serve as the data management center for this clinical trial, with responsibilities as follows:

- (1) To be responsible for the statistical design of the clinical trial;
- (2) To provide statistical requirements for the design of the Case Report Forms (CRFs) and participate in the revision of the CRFs;
- (3) To complete the randomization process and blinding design according to the research requirements, and assist researchers in implementing the blinding;
- (4) To complete the randomization process according to the research requirements;
- (5) To be responsible for developing the Data Management Plan (DMP), organizing data entry, data checking, and management;
- (6) To be responsible for developing the Statistical Analysis Plan (SAP), completing statistical analysis and reporting of results;
- (7) To be responsible for developing the Study Monitoring Plan (SMP), completing the monitoring of the entire study;
- (8) To be responsible for regularly submitting data and safety reports to the Data Safety Monitoring Board (DSMB).

## **6 Phase Ib Protocol**

### **6.1 Objectives**

#### **Primary objectives:**

1. To observe the safety and tolerability of 1-3 doses of 2 mg or 4 mg DNA vaccine in healthy volunteers.
2. To observe the safety and tolerability of a combined immunization regimen consisting of three doses of 2 mg or 4 mg DNA vaccine followed by one dose of rTV vaccine in healthy volunteers.

#### **Secondary Trial Objectives:**

To preliminarily evaluate the immunogenicity of the combined immunization regimen consisting of three doses of 2 mg or 4 mg DNA vaccine followed by one dose of rTV vaccine in healthy volunteers.

### **6.2 Endpoint Events**

Study endpoint events are the endpoint expected to be observed in the clinical trial. Results of the clinical trial will be analyzed using the frequency of endpoint events.

#### **6.2.1 Primary Endpoint Events**

##### **6.2.1.1 Primary Safety Endpoint Event**

During the clinical trial, the safety indicators are graded according to Annex 2, and the following are the primary safety endpoint events:

- (1) Grade 3 or higher local adverse reactions;
- (2) Grade 3 or higher systemic adverse reactions;
- (3) Any events of immunization regimen termination caused by vaccine problems;
- (4) Any event leading to the discontinuation of the immunization schedule due to vaccine-related issues.

##### **6.2.1.2 Primary immunogenicity endpoint event**

The HIV-specific T-cell immune response was measured using the ELISPOT method at 2, 4, 8, 12, 16, 20, and 24 weeks following the last vaccination.

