### **2.1 DNA Vaccine**

#### **2.1.1 Research of AIDS DNA vaccine**

DNA vaccines have been shown to induce HIV- and simian immunodeficiency virus (SIV)-specific cytotoxic T lymphocytes (CTL), T-cell proliferative responses, and antibodies in mice and primates, and to protect chimpanzees from HIV infection [20-21]. In a phase I clinical trial of an HIV DNA vaccine conducted by the University of Oxford, 18 HIV-negative healthy volunteers were administered two intramuscular injections of the vaccine at two DNA doses (100 or 500 micrograms) three weeks apart. The results demonstrated that both doses were well tolerated in humans [22]. A preliminary trial of a DNA vaccine by the National Institutes of Health (NIH) in the United States indicated that a single injection of a 3 mg dose of DNA caused mild and rare adverse reactions [23]. In a phase I clinical trial organized by the U.S. AIDS Vaccine Evaluation Group, multiple injections of a 3 mg DNA dose at months 0, 1, 3, and 6 were well tolerated by all 52 volunteers and induced antigen-specific cell proliferation and chemokine production [24]. In a recent human trial organized by Merck, the safety of 1 mg and 5 mg DNA vaccine doses was explored, with two different adjuvants used in the 5 mg group, and immunizations administered at weeks 0, 4, 8, and 26. The company reported its findings at the HIV Vaccine Trials Network meeting in May 2003: the 5 mg DNA dose was well tolerated; and by week 12 post-immunization, the CTL response induced by the 5 mg dose was significantly stronger than that induced by the 1 mg dose [25].

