### 2.2.2 Recombinant vaccinia virus vaccine

The vaccinia virus vector vaccine of this study is called recombinant vaccinia virus (rTV) AIDS vaccine, with the vector using Tiantan vaccinia strain 752-1, and is provided by Beijing Institute of Biological Products Co., Ltd. This Tiantan strain of vaccinia virus has been used in smallpox vaccine and extensively vaccinated in China.

The rTV vaccine expressed HIV genes are the main popular B'/C recombinant strain CN54 from China. The env (gp140TM), gag and pol genes act as the target genes and are inserted into TK region of vector. These HIV genes have been transformed to ensure the safety and immunogenicity of the vaccines.

We have manufactured 50,000 doses of rTV vaccines in compliance with GMP conditions, and all items are tested qualified and the test results are shown in Annex 5. Main information of rTV vaccine is shown in Table 2.

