| Is there a qualitative or quantitative difference in the immune responses elicited by different doses of the DNA vaccine when boosted with the same dose of the recombinant vaccinia virus vaccine? | Antigen-specific ELISPOT and antibody responses will be measured at weeks 2, 4, 8, and 24 after the last vaccination.                                            |

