| HBsAg and HCV antibody                               | X  |     |   |   |     |   |   |     |   |    |     |                |    |    |    |    |    |    |    | X              |
| Syphilis test                                        | X  |     |   |   |     |   |   |     |   |    |     |                |    |    |    |    |    |    |    | X              |
| Urine pregnancy                                      | X  | X   |   |   | X   |   |   | X   |   |    | X   |                |    |    |    | X  | X  | X  | X  | X              |
| DNA/ANA antibody                                     | X  |     |   |   | X   |   |   | X   |   |    | X   |                |    |    |    |    |    |    |    | X              |
| Immune function                                      | X  |     |   |   |     |   |   |     |   |    | X   |                |    |    |    |    |    |    |    | X e |
| HLA typing                                           |    | X   |   |   |     |   |   |     |   |    |     |                |    |    |    |    |    |    |    |                |
| HIV antigen specific antibody (ELISA) d              |    | X   |   |   | X   |   | X | X   |   | X  | X   |                |    | X  | X  | X  | X  | X  | X  | X              |
| HIV cellular immune response (ELISPOT)               |    | X   |   |   | X   |   | X | X   |   | X  | X   |                |    | X  | X  | X  | X  | X  | X  | X              |
| HIV intracellular staining (ICS)                     |    | X   |   |   | X   |   | X | X   |   | X  | X   |                |    | X  | X  | X  | X  | X  | X  | X              |
| HIV neutralizing antibody d                          |    | X   |   |   | X   |   | X | X   |   | X  | X   |                |    | X  | X  | X  | X  | X  | X  | X              |

|                                 |   |  |  |  |  |  |  |  |  |   |   |   |   |   |   |   |   |   |   |
|---------------------------------|---|--|--|--|--|--|--|--|--|---|---|---|---|---|---|---|---|---|---|
| Vaccinia antibody        | X |  |  |  |  |  |  |  |  | X |   |   | X | X | X | X | X | X | X |
| Vaccinia viremia testing |   |  |  |  |  |  |  |  |  |   | X | X | X | X |   |   |   |   |   |

Notes:

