### 6.6.2 Cellular Immune Response

#### ELISPOT Assay:

- Performed using freshly isolated PBMCs from blood samples.
- Stimulation is conducted using peptide pools of Env, Gag, Pol, and Nef.
- Experimental results are measured using an automated plate reader.

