### (4) Immunogenicity Evaluation:

Immunogenicity evaluation will primarily be descriptive, reporting the positive rates of humoral and cellular immune responses.

For the Phase Ib study, differences in immunogenicity among different vaccination doses (combined immunization vs. DNA-alone), smallpox vaccination history, and study groups (vaccine vs. placebo) will be compared using logistic regression. The outcome variable (Y) will be the presence or absence of humoral/cellular immunity, with independent variables including vaccination dose (high vs. low), immunization strategy (combined vs. DNA-alone), smallpox vaccination history (vaccinated vs. unvaccinated), and study group (vaccine vs. placebo). For immune response intensity indicators such as antibody titers and Elispot counts, repeated measures ANOVA will be used. If the data do not meet the conditions for repeated measures ANOVA, appropriate data transformations will be applied.

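### The immunogenicity endpoints use only samples taken after rTV or its placebo, so prime and boost are separated through one 12 v 6 contrast at 4 mg and not at all at 2 mg

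*Protocol*

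**What the plan says.** - **Endpoint window.** Protocol 6.2.1.2 has the primary T-cell response "measured using the ELISPOT method at 2, 4, 8, 12, 16, 20, and 24 weeks following the last vaccination". Section 6.2.2 uses the same seven times for antibodies and cytokines.
- **Last vaccination.** By 6.4.2 and Table 5 this is rTV in both combined arms, rTV placebo in the DNA-only arm and placebo in the placebo arm.
- **Sampling.** The Table 6 row "HIV cellular immune response (ELISPOT") is also marked at weeks 0, 4, 6, 8, 10 and 12, and Table 7 draws blood for it at each of these weeks.
- **Antigens.** Table 1 gives the DNA vaccine env, gag, pol and nef. Section 2.2.2 says of rTV that, besides env, "gag and pol genes act as the target genes and are inserted into TK region of vector"; Table 2 likewise lists no nef. For the ELISPOT assay, 6.6.2 states: "Stimulation is conducted using peptide pools of Env, Gag, Pol, and Nef".
- **Analysis.** Section 6.10.5 (4) plans a logistic regression: "The outcome variable (Y) will be the presence or absence of humoral/cellular immunity". Its terms include dose, combined versus DNA-alone, smallpox vaccination history, and vaccine versus placebo.
- **Question asked.** Table 3 poses the primary immunogenicity question as "Is there a qualitative or quantitative difference in the immune responses elicited by different doses of the DNA vaccine when boosted with the same dose"; rTV is the common boost.

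**The concern.** The plan tests both DNA dose and combined versus DNA-alone immunization. Both tests need some view of what the DNA prime did before rTV was given. The endpoints contain none, although the assay is run at those weeks.

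At 4 mg the DNA-only arm fills the gap, but with six people. At 2 mg nothing fills it: a post-boost response in the low-dose arm cannot be divided between prime and boost, and a post-boost difference between doses cannot be checked against the difference already present before the boost.

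The antigen mismatch bears on the same small contrast. rTV cannot raise a Nef response directly. If a Nef-only responder counts as positive, the combined and DNA-only arms gain positives that say nothing about the boost, and the difference between them shrinks.

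**Working it through.** Weeks are on the participant's own clock in Table 6 (first dose at week 0). Table 5 shows the 4 mg arms two weeks later.

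**1. Which samples are endpoints.** With rTV or its placebo at week 12, the endpoint weeks are 12 + {2, 4, 8, 12, 16, 20, 24} = {14, 16, 20, 24, 28, 32, 36}. These match the Table 6 ELISPOT columns after rTV. The third DNA dose is at week 8, so weeks 10 and 12 are 2 and 4 weeks after it and belong to no endpoint. The first endpoint sample, week 14, is 14 − 8 = 6 weeks after the third DNA dose.

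**2. What the groups identify.** Arm sizes are 12 + 12 + 6 + 6 = 36. By 6.10.3, phase one randomizes DNA-L+rTV and placebo 2:1 (12 and 6), and phase two randomizes DNA-H+rTV and DNA-only 2:1 (12 and 6). Take an intercept and terms for vaccine, strategy and dose:

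| Group | Intercept | Vaccine | Strategy (combined) | Dose (high) |
|---|---|---|---|---|
| DNA-L+rTV | 1 | 1 | 1 | 0 |
| DNA-H+rTV | 1 | 1 | 1 | 1 |
| DNA-only | 1 | 1 | 0 | 1 |
| Placebo | 1 | 0 | 0 | 0 |

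The matrix has rank 4 of 4. Its inverse gives:
- strategy = DNA-H+rTV − DNA-only;
- dose = DNA-H+rTV − DNA-L+rTV;
- vaccine = (DNA-L+rTV − placebo) − (DNA-H+rTV − DNA-only).

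The boost effect at 4 mg is therefore identified by a randomized contrast. The vaccine term, which stands for 2 mg DNA alone, is obtained by subtracting the 4 mg boost effect from the 2 mg arm, so it assumes the same boost at both doses. Without that assumption, phase one alone has rank 2 for three terms (intercept, DNA, rTV).

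**3. Precision of the one contrast.** Exact Fisher power for 12 v 6 at 0.05 (two-sided assumed). Fisher's test stands in for the planned regression, and the response rates are assumed because the protocol gives none.

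| DNA-H+rTV v DNA-only | Power |
|---|---|
| 90% v 20% | 0.83 |
| 80% v 20% | 0.64 |
| 80% v 30% | 0.46 |
| 70% v 30% | 0.28 |

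**4. Dilution by Nef.** Suppose Env/Gag/Pol positivity is a v b and Nef positivity is q in both 4 mg arms, independent of the other pools. Any-pool positivity is 1 − (1 − a)(1 − q) against 1 − (1 − b)(1 − q), so the difference is (a − b)(1 − q). With a = 80% and b = 20%:

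| Nef rate q | Any-pool rates | Difference (points) | Power |
|---|---|---|---|
| 0% | 80% v 20% | 60 | 0.64 |
| 10% | 82% v 28% | 54 | 0.53 |
| 20% | 84% v 36% | 48 | 0.44 |
| 30% | 86% v 44% | 42 | 0.35 |
| 50% | 90% v 60% | 30 | 0.21 |

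If instead every Nef responder also responds to Env, Gag or Pol, the rates stay at 80% v 20% and nothing is lost.

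**5. What the pre-boost samples add.**
- At weeks 10 and 12 the phase-one arms differ only in 2 mg DNA against placebo (12 v 6, randomized), so the 2 mg prime can be read directly.
- For dose, 12 + 6 = 18 participants have had 4 mg, against 12 at 2 mg. The variance factor is 1/18 + 1/12 = 0.139, against 1/12 + 1/12 = 0.167 after the boost. That is 17% less variance, or about 9% less standard error.
- For the boost contrast on ELISPOT counts, adjusting for week 12 reduces residual variance by r²: 9% at an assumed correlation of 0.3 and 49% at 0.7, before the loss of one degree of freedom (12 + 6 − 2 = 16 becomes 15).

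**The case against.** The best defence is that the endpoint answers the question asked. The immunogenicity objective in 6.1 concerns the combined regimen, and Table 3 asks about DNA dose under a common boost. The aim on one to three DNA doses is safety only. Post-boost timing fits this, and a Nef response in someone given DNA and then rTV is a real response to the regimen. This stands for the primary question, which is why the prime reading belongs among the secondary endpoints. It does not cover the combined versus DNA-alone term that 6.10.5 also plans.

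Stronger readings that a reader might infer, and that the protocol does not support:
- **That the endpoint cannot separate prime from boost at all.** The DNA-only arm receives the same 4 mg DNA plus rTV placebo, is randomized against DNA-H+rTV, and shares its clock. The boost is isolated at 4 mg.
- **That the protocol counts Nef responders as positive.** It lists the pools but gives no rule for combining them. Table 3 speaks of antigen-specific ELISPOT, and a positivity rule may properly sit in an SAP that is not shown. The Nef point is therefore conditional.
- **That the pre-boost data are discarded.** They are collected, and 6.10.5 does not restrict its repeated measures analysis to particular weeks. They are simply not endpoints.
- **That the cited DNA trial proves week 12 is the right time.** Section 2.1.1 reports that "by week 12 post-immunization, the CTL response induced by the 5 mg dose was significantly stronger" than that from 1 mg, but two adjuvants were used in the 5 mg group, the doses are not 2 and 4 mg, and the starting point of the clock is unclear.

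Independence of Nef is also doubtful, because one plasmid carries gag, pol and nef as a fusion gene.

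**Conclusion.** The point holds in a limited form. The immunogenicity endpoints in 6.2 separate prime from boost only through 12 v 6 at 4 mg. At 2 mg they do not separate them, unless the boost effect is assumed equal at the two doses. This follows from the schedule and allocation alone.

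The Nef effect depends on reading cellular immunity across all four pools. It then dilutes the contrast; it neither biases it in favour of either arm nor makes it unidentifiable. Its size is illustrative: power falls from 0.64 to between 0.53 and 0.21 for independent Nef rates of 10% to 50%, and does not fall if Nef responders are already positive on another pool.

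The gain for the dose comparison is small (about 9% in standard error). That comparison is also not randomized either before or after the boost, because the two doses are enrolled in successive phases. In a mainly descriptive study of 36 people this is a worthwhile refinement that costs almost nothing. It is not a flaw that invalidates the primary endpoint.

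**What to change.** 1. In 6.2.2, add ELISPOT at weeks 10 and 12 (2 and 4 weeks after the third DNA dose) as a secondary DNA-prime endpoint by dose. State that the week 12 sample is drawn before rTV or its placebo. Note that 2 mg v placebo is randomized and 2 mg v 4 mg is not.
2. In 6.10.5 (4), analyse the boost contrast (DNA-H+rTV v DNA-only) on the Env, Gag and Pol pools, with the week 12 pre-rTV value as covariate for ELISPOT counts. Use this covariate for the boost contrast only. In the dose comparison the week 12 value is itself a result of dose, and adjusting for it would remove part of the effect sought.
3. Report Nef separately, as a response that rTV should not raise directly.
4. While 6.2 is open, reconcile its seven post-vaccination times with Table 3, which says: "Antigen-specific ELISPOT and antibody responses will be measured at weeks 2, 4, 8, and 24 after the last vaccination".

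The cost is wording, slightly more analysis and one more secondary endpoint. All the samples and pools are already scheduled.
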